## Abstract

**Background:**

The Ukrainian crisis, sparked by the Russian invasion, has generated one of the most extensive refugee crises in modern history. Addressing the mental health challenges of Ukrainian refugees is critical to promoting their resilience and successful integration into host communities. Traditional support group interventions might be challenging to implement for geographically dispersed populations, making the metaverse an innovative and inclusive platform for providing much-needed support to such populations.

**Methods/design:**

Displaced Ukrainian refugee adults (18 years or older) without current psychiatric diagnoses or current involvement in therapeutic interventions are included in the study. Participants are randomized to one of three conditions: (1) Metaverse Support Groups, (2) In-Person Support Groups, or (3) Waitlist. Both intervention groups (Metaverse and In-Person) undergo 5 support group sessions, and data are collected at baseline, mid-intervention, post-intervention, and 3-month follow-up. Primary outcomes are depressive symptomatology and anxiety. Secondary outcomes are perceived social support, well-being, and gender-based violence awareness.

**Discussion:**

To our knowledge, this is the first attempt to test the efficacy of support groups in the Metaverse for the Ukrainian refugee population. This study can thus add substantially to the body of knowledge on effective interventions and policies for refugees.

**Trial registration:**

ClinicalTrials.gov Identifier: NCT06142032 (https://clinicaltrials.gov/study/NCT06142032). Registered on November 8, 2023.

**Supplementary Information:**

The online version contains supplementary material available at 10.1186/s13063-024-08543-6.

## Background

The ongoing conflict in Ukraine has led to a significant number of displaced individuals seeking refuge in various countries, leading to one of the most pervasive conflict-based humanitarian crises in Europe since World War II. At the time of this writing, it is estimated that more than 6.2 million people have left Ukraine to seek refuge, from which more than 5.8 million are recorded in Europe [1]. Pre-migration and post-migration factors, such as trauma, loss, war violence, separation, lack of support networks, and psychosocial difficulties with adjustment in the host country, have been associated with increased susceptibility to mental health problems and poorer well-being for internally displaced Ukrainian refugees. Previous studies have shown associations with post-traumatic stress disorder, anxiety, depression, sleep disturbances, anger, and decreased quality of life [2–4]. Additionally, with restrictions imposed for the male population to leave the country, refugee communities are mostly comprised of women, with studies highlighting their increased vulnerability [3]. As previous ecological models have shown, ongoing stressors in refugees’ social ecology and displacement-related stressors have big effects on their mental health and well-being [5]. Addressing the mental health challenges of Ukrainian refugees is critical to promoting their resilience and successful integration into host communities.

Over the years, formally established support groups have proven their value for individuals’ well-being and mental health on the simple premise that people who share similar difficulties and stressors may understand one another better [6]. Support groups are an inexpensive and convenient, yet effective ways to receive support. Studies show a consistent pattern of the effectiveness of professionally-facilitated support groups for people struggling with mental illness [7]. Additionally, peer support groups as community-based interventions have been proven to be effective in addressing the psychosocial and mental health needs of refugees [8], with several studies showing improvements in their mental health, well-being, and psychosocial management [8].

However, traditional support groups for refugees come with some limitations: (1) interventions might be challenging to implement for geographically dispersed populations, (2) logistical constraints, (3) stigma associated with seeking support within a community or in-person setting may deter some individuals from participating or to meaningfully participate, (4) reduced flexibility in terms of accessibility, (5) cultural and linguistic limitations, and (6) lack of anonymity, which can inhibit open communication and deter individuals from seeking support due to fear of judgment or stigma [9–13].

In this context, increasing social support accessibility for Ukrainian refugees who struggle with mental health and psychosocial challenges is critical.

### Framework and rationale for the study

In recent years, online support groups have gained popularity, allowing for a more flexible and accessible way to facilitate mental health and psychosocial support. Several studies indicated that online chat support groups have a positive impact on mental health and well-being through empowerment [6], stigma—reduction [14], and peer support [6].

However, the vast majority of online support groups are un-moderated, very few of them are facilitated by a mental health specialist, or have a compelling raison d’être behind them, and very few of them have ever been tested in randomized clinical trials. Thus, it is largely unclear if they are as beneficial as traditional support groups or, perhaps, more importantly, if they might have unintended side effects (e.g., social avoidance). Additionally, to our knowledge, none has provided comprehensive evidence-based support for their efficacy on refugees. The technology format used for most support groups is either text-based (online group chats/forums on social media platforms) or through video conferencing platforms (e.g., Zoom). While these types of technological means may facilitate accessibility and flexibility, and manage geographical, cultural, and linguistic constraints, they may not provide full anonymity or may not have the potential to meaningfully re-create in-person environment and social cues.

There is a strong line of research showing the beneficial therapeutic effects of virtual reality therapy (VR therapy) [15]. Studies have shown that VR exposure therapy is efficient in treating post-traumatic stress disorder [15–17], phobias [15, 17, 18], substance-related disorders [15, 17], eating disorders [15, 17], psychosis [17], and even autism spectrum disorders [17]. In addition, evidence suggests that, compared to in-person interventions, VR-based group therapy can foster a sense of social presence and connection among participants, leading to an improvement in treatment outcomes [19].

More recently, the emergence of the metaverse has provided an exciting development for mental health support strategies [20]. While the evidence on the effectiveness of interventions delivered in the metaverse is still in its infancy, a few pilot studies have shown that applying metaverse-related technologies to deliver mental health programs for sexual dysfunctions, autism spectrum disorder, and eating disorders yields promising results [21–23].

### Objectives

The primary aim of this study is to evaluate the efficacy of Metaverse virtual support groups in improving the overall well-being of Ukrainian refugees. Secondary objectives include (1) understanding how virtual spaces impact Ukrainian refugees perceived social support and (2) whether such platforms can increase awareness of gender-based violence.

We aim to examine whether the eventual improvements observed in the active intervention groups are attributable to the interventions themselves rather than simply the passage of time. Therefore, we will compare the outcomes not only between the active intervention conditions but also with the waitlist control group, who are assessed similarly to the other groups but do not receive any intervention.

This study is critical in the current landscape for several reasons. Firstly, the metaverse offers a scalable way to reach a larger population of refugees who may be dispersed across various geographical locations, breaking the barriers of distance and time. Secondly, the anonymity provided by virtual environments may encourage more open dialogue about sensitive or stigmatizing issues, potentially leading to disclosures on sensitive topics and more effective emotional support and coping strategies. Lastly, utilizing immersive technology allows for a culturally and linguistically tailored approach, providing refugees not just with generic aid but with nuanced, community-specific support.

### Trial design

This protocol outlines a randomized clinical trial conducted to assess the efficacy of virtual support groups (i.e., groups meeting in the Metaverse) for Ukrainian refugees. The participants are randomly assigned to one of three conditions: (1) In-Person intervention group; (2) Metaverse intervention group; and (3) Waitlist. Stratification will consider factors such as age, gender, and trauma, to achieve balanced group distributions.

Major assessments are at baseline, mid-intervention, post-intervention, and 3-month follow-ups.

Our trial follows an equivalence framework and has a 1:1 allocation ratio, meaning participants are evenly distributed between the intervention and control groups.

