#### Secondary outcomes

Well-being, gender-based violence awareness, and perceived social support constitute the secondary outcomes.

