#### Sample size

An a priori power analysis based on a medium effect size estimation [37, 38] indicated that a total of 45 participants are needed (planned main statistical test is ANOVA repeated measures, within-between interaction; *f* = 0.25; statistical power = 0.95; *α* error probability = 0.05; three groups, four main measurements (pre-intervention, mid-intervention, post-intervention, and follow-up). Power analysis was computed using the G*Power 3.1 program [39].

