The improvement in the mental health and well-being scores within and between the groups will be examined using mixed-effects linear regression with a random intercept and slope over time (three assessments: baseline, after session 2, and post-treatment) and fixed effects for treatment assignment. The 3-month follow-up data will be analyzed using linear mixed effects model that incorporates random intercepts for participants and facilitators. Additionally, we may consider including random slopes for time if the data structure warrants it. If ICC analyses will indicate the presence of a hierarchical structure, we will proceed with conducting multilevel analyses. In addition, we will incorporate fixed effects for time and intervention condition and include any necessary covariates. We intend to perform longitudinal analyses in order to ascertain the long-term effects of the intervention. To evaluate changes in outcome measures from the initial measurement to each subsequent assessment, we plan to employ repeated measures ANOVA, where the data is complete, or mixed effects models, where data is incomplete. Moreover, we acknowledge that the linear mixed-effects model allows for the inclusion of covariates (we plan to control for demographics), and this flexibility makes it a robust alternative to repeated measures ANOVA, especially in complex datasets. The use of covariates was taken into account appropriately in the mixed-effects model, which is another reason we plan this approach when dealing with missing or incomplete data. The results of the other measures—demographic variables and therapeutic alliance as potential moderators and mediators—will be examined in an exploratory manner, utilizing regression models or mediation analyses. The error probability and the issue of multiple testing will be addressed either by employing the Bonferroni correction or the false discovery rate correction. Missing data—over 5%—will be handled with multiple imputation methods. Oversight and monitoring of the data collection process is conducted by the principal investigator and the project manager. Check-in regular meetings are held to review the progress of data collection, address any issues that may arise, and ensure compliance with the study protocol and ethical guidelines.

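### The protocol labels the trial an equivalence trial, but its aim, main test and sample size are built to detect a difference, and about 15 per arm cannot support an equivalence conclusion

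*Protocol article*

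**What the plan says.** The framework is declared once, under Trial design: "Our trial follows an equivalence framework and has a 1:1 allocation ratio". The sentence continues "meaning participants are evenly distributed between the intervention and control groups", which explains the allocation and not the equivalence. That section does not say which arms would be equivalent, on which outcome or within what limits.

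The other sections point elsewhere:

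- **Objectives:** "The primary aim of this study is to evaluate the efficacy of Metaverse virtual support groups in improving the overall well-being of Ukrainian refugees". The same section wants to separate the effect of the interventions from the passage of time, and says "we will compare the outcomes not only between the active intervention conditions but also with the waitlist control group".
- **Sample size:** "An a priori power analysis based on a medium effect size estimation" led to 45 participants. The inputs are f = 0.25, power 0.95, alpha 0.05, three groups and four measurements. The "planned main statistical test is ANOVA repeated measures, within-between interaction".
- **Data collection, management, analysis:** "The improvement in the mental health and well-being scores within and between the groups will be examined using mixed-effects linear regression", with repeated-measures ANOVA where data are complete.

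On outcomes, the Primary outcomes section names depressive symptoms and anxiety, as change in total score from baseline to post-intervention. The next section says "Well-being, gender-based violence awareness, and perceived social support constitute the secondary outcomes".

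**The concern.** The framework fixes the null hypothesis. In an equivalence trial the null is a difference at least as large as a stated margin, and the trial succeeds when the confidence interval lies inside that margin. The interaction test named under Sample size has the opposite null, no difference in change between groups. If it is not significant, it has failed to find a difference, which is not evidence that two formats perform alike. Equivalence is also the wrong question for either comparison with the waitlist, since showing an intervention equivalent to no intervention would defeat the efficacy aim.

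At stake is what may be concluded about Metaverse against In-Person groups. Under an equivalence label, a reader could take a null result between the two formats as showing that they are interchangeable, and the trial is too small to show that at any but a very wide margin.

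A second, separate inconsistency concerns the aim: the primary objective is framed as well-being, while the primary outcomes are depression and anxiety.

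**Working it through.** **1. Reproduce the sample size as a test of difference.** From Sample size: f = 0.25, k = 3 groups, m = 4 measurements, alpha = 0.05, power 0.95. The article gives no correlation between repeated measures and no sphericity correction; I assume rho = 0.5 and epsilon = 1.

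- Noncentrality: lambda = f² × N × m × epsilon / (1 − rho) = 0.0625 × 45 × 4 / 0.5 = 22.5
- df1 = (k − 1)(m − 1) = 6; df2 = (N − k)(m − 1) = 42 × 3 = 126
- Power at N = 45: 0.955. The smallest N reaching 0.95 is 44 (power 0.951), which becomes 45 with equal arms.

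The stated 45 is therefore reproduced as a pure difference calculation. It depends on rho: the smallest N is 61 at rho = 0.3 and 28 at rho = 0.7. No margin enters the formula.

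**2. Precision for Metaverse minus In-Person.** Equal allocation gives 45 / 3 = 15 per arm. Work in SD units of the outcome; r is the assumed correlation between baseline and post-intervention scores.

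- 90% half-width, unadjusted: t(0.95, 28) × √(2/15) = 1.701 × 0.365 = 0.62 SD
- 95% half-width, unadjusted: 2.048 × 0.365 = 0.75 SD
- Baseline-adjusted, 90%: t(0.95, 27) × √(2/15 × (1 − r²)) = 0.54 SD at r = 0.5 and 0.44 SD at r = 0.7

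**3. Chance of showing equivalence if the two formats are truly identical.** Two one-sided tests, each at 0.05, 15 per arm. The margins are assumptions.

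| Assumed margin | Unadjusted | Adjusted, r = 0.5 | Adjusted, r = 0.7 |
|---|---|---|---|
| 0.5 SD | 0.6% | 4% | 19% |
| 0.8 SD | 38% | 59% | 82% |

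Unadjusted, 80% power needs a margin of about 1.10 SD and 95% power about 1.35 SD. Scaling 1.10 by √(1 − r²), the 80% margin is about 0.95 SD at r = 0.5 and 0.78 SD at r = 0.7. In the other direction, unadjusted 80% / 95% power needs 70 / 105 per arm at a 0.5 SD margin and 28 / 42 per arm at 0.8 SD.

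**4. Power of a single pairwise contrast.** This matters for the fix. For a two-sided test at 0.05 with 15 per arm and an assumed true difference of 0.5 SD:

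- Unadjusted: noncentrality 0.5 / 0.365 = 1.37, power 0.26
- Adjusted at r = 0.5: 1.37 / √0.75 = 1.58, power 0.33

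The 0.95 under Sample size belongs to the three-arm, four-time-point interaction and does not carry over to one pair of arms.

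**The case against.** The strongest reply is that this is one loose word. Equivalence appears once, in the sentence on allocation, and what follows speaks only of even distribution. The rest of the article consistently speaks of efficacy, and the group-by-time test addresses efficacy. This is a plausible reading and it stands. It makes relabelling the natural remedy, but the label is still wrong. Nor can a real interest in comparability be ruled out: the rationale asks whether online groups do as much good as traditional ones, and the Objectives plan a comparison of the two active arms.

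A second reply is that a margin or interval rule may sit in an analysis plan not shown here. That is fair as to the margin itself, and its absence from the article is not the point. But a margin is an input to an equivalence sample size, and the stated inputs contain none. A margin set later would not turn 45 into a number derived for equivalence.

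A third reply is that the margins above are assumed and that the planned mixed models use more data than a two-sample comparison. Both are true. The figures are illustrative, which is why adjusted values are shown beside the unadjusted ones.

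A reader might go further and infer that the investigators intend to report a null result between formats as equivalence, or that the trial's main claim fails. The article supports neither. Its main claim is efficacy, and no section plans to read non-significance that way. The risk lies in a reading that the label invites.

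**Conclusion.** The contradiction is real. The declared framework does not match the efficacy objective, the main test, the sample-size basis or the analysis. As designed, the trial cannot support an equivalence conclusion between Metaverse and In-Person at margins such as 0.5 SD: the 90% half-width is about 0.62 SD (0.54 SD adjusted at r = 0.5), and 80% power needs a margin near 1.1 SD unadjusted. These figures assume 15 analysed per arm, a true difference of zero, independent participants and margins of my choosing.

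The sample size itself is not arithmetically wrong; 45 is right for the interaction test under rho = 0.5. The article states no formal hypothesis, so the superiority reading rests on the efficacy aim and the chosen test. The mismatch between the well-being aim and the depression and anxiety outcomes is a separate point that holds whatever the framework is called.

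**What to change.** 1. Under Trial design, replace equivalence framework with superiority framework and keep the allocation statement separate.
2. State that Metaverse versus In-Person will be reported as an estimate with a 95% confidence interval, and that a non-significant difference will not be read as equivalence or non-inferiority.
3. Under Objectives, make depressive and anxiety symptoms the primary aim and well-being a secondary one, to match the outcome sections.

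These are wording changes and need no extra participants. The cost is a narrower claim about how the two formats compare.

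If equivalence was truly intended, relabelling is not the answer. The plan would then need the pair of arms and the outcome named, a justified margin, a confidence-interval or two-one-sided-tests rule, and a restated sample size; 45 does not deliver it at the margins examined above.

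If the sponsor also names a pairwise primary contrast, such as Metaverse versus Waitlist from baseline to post-intervention, that is a substantive amendment, because Trial status puts the start of recruitment in December 2023. The amendment should say that the 0.95 power applies to the three-arm interaction and that the power of the pairwise contrast is about 0.26 to 0.33 at 0.5 SD.

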## Methods

### Study setting

The design of this study complies with the Consolidated Standards of Reporting Trials (CONSORT) guidelines [24] and follows the Standard Protocol Items: Recommendations for Interventional Trials (SPIRIT) Statement 2013 [25] (see also Additional file 1 and Table 1).

**Table 1 Tab1:**
[figure not shown]
SPIRIT figure—schedule of enrollment, interventions, and assessments

The study population consists of Ukrainian refugees. The study is being implemented in collaboration with NGOs working with Ukrainian refugees.

### Eligibility criteria

Adult Ukrainian refugees (18 years or older) who are not formally diagnosed with a mental disorder, do not have scores suggestive of PTSD, and are not currently participating in any ongoing therapeutic intervention or mental health treatment were included.

### Interventions

Our research team designed the intervention protocol following evidence-based practices for support groups, specifically drawing from Cognitive Behavioral Therapy (CBT) principles [26]. Additionally, the protocol is based on guidelines from the United Nations High Commissioner for Refugees [27], Inter-Agency Standing Committee (IASC, 2007), the World Health Organization [28], and the Finish Refugee Council for support groups working with refugees [29]. Our intervention adopts a trauma-informed approach, acknowledging the unique and complex needs and experiences of individuals who have been exposed to traumatic events. The language used for the intervention sessions is Russian. This decision was made in consultation with previous Ukrainian refugees that the team worked with, as it is the preferred and most used language among this community. This language choice was deliberate to enhance inclusivity, allowing us to enroll a broader range of participants who could benefit from the intervention. To ensure agreement and comfort with the language choice, we included a question tapping into this, at the beginning of the screening process. We have observed no dropouts due to language concerns so far, supporting the argument for the effectiveness of our language inclusivity approach.

Both the Metaverse and In-Person conditions undergo a 1.5-h session each week for 5 weeks. Licensed psychotherapists facilitate both intervention conditions and follow the same protocol structure, which aims to improve the mental health and well-being of Ukrainian refugees and deliver psychoeducation on mental health and gender-based violence.

For both intervention conditions, the program has the following structure: (1) intake and the baseline assessments (described below) are conducted, (2) sessions 1 and 2, (3) mid-program assessment, (4) sessions 3, 4, and 5, (5) final assessment, (6) 3-month follow-up.

The general structure of a session is as follows: (1) *Introduction and Welcome*—a brief welcome and introduction to set the tone for the session, review of confidentiality and respectful communication guidelines, and group rules; (2) *Check-in*—participants share how they are feeling and briefly update the group on their current situation or experiences; (3) *Addressing the topic of discussion*; (4) *Sharing and support*—participants are encouraged to share experiences, thoughts, and feelings related to the topic of discussion, while group members provide supportive feedback, validation, and empathy to each other; (5) *Psychoeducation*—brief educational component related to the session’s topic, providing information, tools, or resources to enhance coping and resilience; (6) *Closure*—summary of the session, key takeaways, homework, reflections on the session, feedback, and next steps.

The Intake aims to assess participants if they are eligible for the study and introduce them to the goals of the program. The baseline assessment is conducted before the first session. A step-by-step guide about accessing and completing the survey is provided. Clarification of any questions or concerns are addressed. Session 1 focuses on facilitating an open discussion on participants’ needs, challenges, and cultural adjustment issues. It aims to create a safe and inclusive environment where participants can share their thoughts, concerns, and experiences, setting the tone for the support program. Session 2 focuses on the overall well-being of Ukrainian refugees and introduces strategies to enhance it. Session 3 focuses on perceived social support aiming at shedding light on its significance in our lives and providing practical tools to strengthen and enhance social networks. Session 4 focuses on mental health, with the aim of deepening participants’ understanding of mental health, reducing stigma surrounding mental health issues, and equipping them with essential knowledge and skills for promoting mental well-being. Session 5 is dedicated to raising awareness about gender-based violence (GBV), its various forms, and its profound impact on individuals and communities. Each session typically consists of 6 to 8 participants. The same 6–8 participants will attend each group session for the specific arm to which they are allocated. Each group will interact with the same members consistently from the first session to the last. Each arm is expected to have a minimum of two groups, and the formation of groups begins once a minimum of six participants have enrolled.

These groups convene weekly. To ensure that participants who miss a session are kept up to date, a briefing is conducted at the beginning of each session. This briefing provides a summary of the previous session’s discussions and activities, allowing all participants to stay informed and engaged, even if they were unable to attend the previous session.

